## **1) Administrative Information**

This document is a supplement to the NORDSTEN-SST protocol, “Comparison of different surgical treatments for Lumbar Spinal Stenosis. A randomized controlled trial comparing the clinical and radiological results using “unilateral laminotomy with crossover”, “bilateral laminotomy” and “spinous process osteotomy” [1].

The SST is one of three arms in the NORwegian Degenerative spondylolisthesis and spinal STENosis (NORDSTEN)- study. The two other arms are Degenerative Spondylolisthesis Trial (DST) and the Observational Cohort (OC).

### **Trial Registration Number**

The trial is registered in ClinicalTrials.gov, first posted december 10, 2013 (Identifier: NCT02007083).

### **Sponsor/ Funding**

The project has received funding from Helse Vest RHF (the Western Regional Health Authority) and Helse Midt RHF (Central Norway Regional Health Authority). The funder has no influence in study design, management and interpretation of data or in decision to submit data.

### **Justification for SAP revision:**

Update January 2016 From the start of inclusion (April 15, 2014) patients with ODI scores less than 25 were excluded. Due to experiences from participating surgeons that a considerable part of the patients was excluded due to ODI less than 25, even if their complaints from leg and back did justify an operation. To enhance the external validity of the study, the steering committee decided that from date 29th August 2015, the patients should not be excluded due to ODI- score lower than 25.

## **2) Introduction**

### **Background and rationale**

The clinical entity “Lumbar Spinal Stenosis” can be defined as a narrowing of the lumbar spinal canal with its contents. This leads to compression of nervous and vascular structures.

The surgical treatment of LSS is to perform a decompression. Several studies have been conducted to compare different posterior decompression techniques. A Cochrane review article from 2015 stated that one cannot conclude which procedure give superior clinical results in these studies[2], Jacobs et al published a review, which includes four previous review papers (among a previous Cochrane-review), and concluded that the scientific evidence was of low or very low quality, and that there was no evidence to recommend one particular surgical method over another, or the extent of decompression needed [3].

Therefore, we plan to perform a multicentre, randomized trial to compare the clinical and radiological results of three midline retaining posterior decompression techniques; “spinous process osteotomy” (SPO), “bilateral laminotomy” (BL), and “unilateral laminotomy with crossover” (UL).

### **Objectives**

#### **Main Objective**

The primary objective is to investigate whether one of the three posterior decompression techniques gives superior results vs the two other surgical methods, and to investigate the extent of decompression needed to sustain good long-term clinical results.

#### **Secondary objectives**

Predictor analysis

To evaluate whether selected radiological parameters and patient characteristics measured at baseline can predict outcomes, and thereby also used to choose the most appropriate treatment.

### 89 **3) Study Methods**

#### 90 Trial design

91 The NORDSTEN-SST is an open label, multicentre randomized controlled trial, with a  
92 superiority design, and three parallel groups. The patients will be randomized into one of three  
93 surgical methods;

#### 94 **Group A) Unilateral laminotomy with crossover (UL)**

95 The laminotomy is first performed ipsilaterally. The decompression of the spinal canal is  
96 initiated by a flavectomy followed by a laminotomy of the lower part of the superior lamina,  
97 and the upper part of the inferior lamina. Laterally, a medial facetectomy is performed and the  
98 patient is then slightly rotated to visualize the contralateral side. The dura is retracted, and the  
99 decompression is performed contralaterally.

#### 100 **Group B) Bilateral laminotomy (BL)**

101 The decompression of the spinal canal is initiated by a bilateral flavectomy followed by a  
102 bilateral laminotomy of the lower part of the superior lamina, and the upper part of the  
103 inferior lamina. Laterally, a medial facetectomy is performed,

#### 104 **Group C) Spinous process osteotomy (SPO)**

105 An osteotomy is performed, at the base of the spinous process above (and sometimes under)  
106 the affected level. The spinous process is retracted to the contralateral side with intact  
107 supraspinal and interspinal ligaments, giving a midline access to the spinal canal. The  
108 decompression is first performed in the midline, then laterally at both sides. A laminotomy of  
109 the lower part of the superior lamina and the upper part of the inferior lamina is performed,  
110 followed by a medial facetectomy. Both nerve roots are visualized, and the lateral recesses are  
111 decompressed. Special attention is warranted when a multilevel decompression is performed  
112 to retain at least 1/3 of the lamina.

113 The SPIRIT checklist [4] has been used as a template for the Study protocol [1]. The reporting  
114 of the trial will be based on an adapted Consolidated Standards of Reporting Trials  
115 (CONSORT) checklist for randomized trials [5].

## **Randomization**

Eligible patients are randomised into one of three arms, unilateral laminotomy with crossover, bilateral laminotomy and spinous process osteotomy with a 1:1:1 allocation. A randomized block design, stratified by hospital and the blocks made as small as possible, is used to ensure equal distribution of all three treatments (randomly selected block size 4 and 6).

Randomisation is performed in the 6 weeks before surgery. The randomisation procedure is concealed and administered by a study coordination centre at a university hospital and communicated to a local research coordinator who is not involved in the treatment of the patients. Randomisation is performed after the patient has signed the informed consent form. The result of the randomisation is documented in the patient record. Hence, neither the patients nor the surgeons can influence the type of intervention.

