## **Sample size**

The trial is planned with a superiority design. The study is designed to detect a difference of 7 ODI-points between the groups. With a standard deviation of 18, a significance level of 0.02, 80% power and a drop-out rate of 15%, we need to include 155 patients in each group. Thus, we plan to include 465 patients over a 4-5 year period. The analysis will be performed according to the intention to treat principles. If the number of drop-out or missing data exceeds 15%, imputation will be performed

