# Norwegian Spinal Stenosis Study Research Protocol

## **Comparison of different surgical treatments for Lumbar Spinal Stenosis. A randomized controlled trial comparing the clinical and radiological results using “spinous process osteotomy”, “bilateral laminotomy” and “unilateral laminotomy with crossover”.**

This is planned to be a multicenter study with 15 participating Norwegian spine centers. The departments of orthopedics at Oslo University hospital and Kysthospitalet i Hagevik, Haukeland University hospital, will be the principal investigators. Two MDs are connected to the study as doctoral students.

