**Statistics:**

We have previously discussed that MCID is around 10-12 ODI-points for this group of patients. This value indicates the individual effect of treatment versus no-treatment. There is today no consensus in the literature of a clinically important difference between treatment groups. We have therefore decided that we want to reveal a difference of 7 ODI-points between the groups. A statistician has calculated a difference of 7 ODI-points between the treatment groups, and in a regular superiority design. Standard deviation is set to 18. Because we have three groups we want to compare the significans-level is lowered from 5% to 2% ( $p = 2$ ). The analyzes in the treatment group is done in the following way: -A compares with B, - A compares with C, -B compares with C.). With 80% power , significans level of 2%, and dropout of 30% n in each group is estimated to 187 (131 + 56). 30% dropout is a high

number, but we are planning to monitor the patients for 10 years, so we must anticipate a high dropout number. If we have problems to achieve 187 in each group, we will settle with 15% dropout. This gives 155 patients in each group.

We will also perform descriptive analyzes. The superiority analyzes is conducted in a One-way Anova system and Post Hoc.

Therefore we are planning to include 561 patients over a 2-3 year period. The analysis is conducted after the Intention To Treat Principle (ITT). Crossovers will be analyzed in the group they were originally randomized into. A sensitivity analysis will be conducted where patient crossing over from one treatment to another will receive the last score before crossover. Dropouts will be registered with the last value before dropout (last value carried forward).

Department of Clinical Research Support, at Oslo University Hospital will provide the block randomisation, and is performed within a computer program called Medinsight. The randomization process cannot be influenced by participating hospitals, and will be performed within 1 month before treatment.

Patient-data, and registration will also be handled by the computer programme called Medinsight.

The research protocol will be registered in [www.clinicaltrials.gov](http://www.clinicaltrials.gov).

The reporting of the trial will be bases on an adapted CONSORT (Consolidated Standards of Reporting Trials) checklist for reporting in randomised trials [18].

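### The SAP's block sizes of 4 and 6 contradict its 1:1:1 allocation to three arms: a block of 4 cannot be balanced, and the fourth slot is not explained

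*Combined protocol and SAP*

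**What the plan says.** SAP section 3, under Randomization: "Eligible patients are randomised into one of three arms", "with a 1:1:1 allocation". The method is a block design, stratified by hospital with the smallest possible blocks, that "is used to ensure equal distribution of all three treatments (randomly selected block size 4 and 6".

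The research protocol, under Statistics, says only that a research support department "will provide the block randomisation, and is performed within a computer program called Medinsight". It gives no block size. Neither document says how three treatments fill a block of four.

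The SAP's Sample size section plans 155 patients in each group, 465 in all. The SAP's Statistical analyses section compares changes by ANOVA with post-hoc tests. It provides for adjustment if descriptive statistics show imbalance, without naming hospital.

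**The concern.** Permuted blocks balance arms exactly only when the block size is a multiple of the number of arms. Six works for three arms; four does not. The SAP's aim of the smallest possible blocks does not fit either, since the smallest balanced block for three arms is 3.

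Two things are at stake. First, a reader cannot tell which scheme was run: a random extra slot, some other rule, or a misprinted block size. The SAP commits to CONSORT-based reporting, and the scheme as written cannot be reported accurately or reproduced. Second, hospital is the only stated stratification factor, and small hospital blocks are the stated means of balancing arms within it. Blocks of 4 weaken that balance, by an amount that depends on the missing rule.

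**Working it through.** **Inputs from the documents**
- SAP, Randomization: three arms, 1:1:1, blocks of 4 and 6, stratified by hospital.
- SAP, Sample size: difference 7 ODI points, SD 18, significance level 0.02, power 80%, drop-out 15%, 155 per group, 465 in total.
- Research protocol, Statistics: 131 evaluable per group; all three pairwise comparisons planned.
- Research protocol, opening paragraph: "This is planned to be a multicenter study with 15 participating Norwegian spine centers".

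**Assumptions**
- Two-sided testing (the documents do not state sidedness; two-sided reproduces their figure).
- 15 hospitals of equal size, 465/15 = 31 patients each.
- Block sizes 4 and 6 equally likely.

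**Step 1. The plan's own sample size**

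n per arm = 2 × SD² × (z₀.₉₉ + z₀.₈₀)² / difference² = 2 × 18² × (2.326 + 0.842)² / 7² = 132.7, so 133, against the protocol's 131.

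The protocol's figure gives 131/0.85 = 154.1, so 155, and 3 × 155 = 465. Starting from 133 gives 133/0.85 = 156.5, so 157. The stated 155 therefore reproduces to within 2 patients. With 155 × 0.85 = 131.75 evaluable per arm, t-test power is 79.2%.

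**Step 2. Divisibility**

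6/3 = 2, so a block of 6 is 2:2:2. 4/3 is not an integer, so a block of 4 that contains all three arms is 2:1:1 in some order. No completed block of 4 is balanced.

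**Step 3. Extra slot drawn at random in each block of 4**

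Each arm is equally likely to receive it, so the expected count is 465/3 = 155 per arm. Simulated trials (1,000 to 2,000 per scheme) compare this with blocks of 3 and 6:

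| | Blocks 4 and 6, random extra slot | Blocks 3 and 6 |
|---|---|---|
| Mean within-hospital gap (largest minus smallest arm) | 1.95 | 1.07 |
| 95th percentile within hospital | 4 | 2 |
| Mean overall gap, of 465 | about 8 | about 4 |
| 95th percentile overall | 15 | 8 |
| Mean power, two smallest arms | 78.6% | 78.9% |
| 5th percentile of that power | 78.0% | 78.6% |

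With blocks of 3 and 6 the within-hospital gap cannot exceed 2, because only the last, incomplete block contributes. With blocks of 4 each completed block can add to it.

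**Step 4. Extra slot always to the same arm, as a bound**

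One block of each size gives that arm 2 + 2 = 4 of 10 patients and each other arm 1 + 2 = 3 of 10. Of 465 that is 186 : 139.5 : 139.5. After 15% drop-out the evaluable numbers are 158.1 : 118.6 : 118.6. T-test power at two-sided 0.02 is then:
- the two smaller arms against each other: 74.2%;
- the larger arm against either smaller arm: 80.5%;
- equal arms, from step 1: 79.2%.

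**The case against.** The strongest reply is that the divisibility error has almost no consequence. The SAP states 1:1:1 and plans 155 per group; a random extra slot or a misprinted number fits that, and a permanently favoured arm does not. With a random extra slot, power differs by about 0.3 percentage points and the mean within-hospital gap by less than one patient in 31. Blocks of 3 and 6 do not guarantee equal totals either, since incomplete blocks leave a mean overall gap of about 4. All of this stands.

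A reader might infer from a block of 4 that the trial ran at about 4:3:3 and lost power. The documents do not support that. It needs the extra slot to go to one fixed arm, which nothing in them suggests, and even then only one of the three comparisons falls to about 74%, while the other two rise slightly.

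A reader might also infer that hospital differences bias the treatment comparison. With a random extra slot, imbalance within hospitals is chance imbalance, which the error rate covers. Leaving the stratification factor out of the ANOVA is a separate matter that arises with any block size.

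The reply does not remove the contradiction. The scheme cannot do what its own sentence says it is for, and nothing elsewhere in the documents resolves it.

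**Conclusion.** The contradiction is certain, because it is arithmetic. Its practical effect cannot be settled from the documents, but under the reading consistent with 1:1:1 it is small: expected allocation is unchanged, power is essentially unchanged, and balance is looser, with overall and within-hospital gaps roughly twice those of blocks of 3 and 6. The sizes rest on 15 equal hospitals and equally likely block sizes; unequal hospitals would change the gaps somewhat. The 155-per-group calculation is unaffected unless the realised arms turn out unequal.

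This is a matter to reconcile and report. The documents show neither bias, nor a loss of power, nor that the realised allocation was unequal.

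**What to change.** 1. Check the central randomisation list and correct the SAP's Randomization section to the block sizes actually generated. If the 4 is a misprint, this closes the point.
2. If blocks of 4 were used, state how the fourth slot was assigned, report realised arm counts overall and by hospital, and include hospital, the stratification factor, in the primary model.
3. If any part of the list is unused, generate it in multiples of 3.

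The SAP's revision note puts the start of inclusion in April 2014, so for patients already randomised the remedy is disclosure and analysis; new block sizes cannot help them. The cost is a check of the list and one line of text, plus, if blocks of 4 were used, one table and one added model term. No new data are needed.

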## **Sample size**

The trial is planned with a superiority design. The study is designed to detect a difference of 7 ODI-points between the groups. With a standard deviation of 18, a significance level of 0.02, 80% power and a drop-out rate of 15%, we need to include 155 patients in each group. Thus, we plan to include 465 patients over a 4-5 year period. The analysis will be performed according to the intention to treat principles. If the number of drop-out or missing data exceeds 15%, imputation will be performed

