## **Statistical analyses**

All statistical analyses will be performed by a statistician blinded to the treatment given. Since this is a large randomized controlled trial, we will likely not need to adjust for potential confounding factors. However, if descriptive statistics reveal that there are imbalances in the study groups we will make comparisons with proper adjustments for such imbalances.

When comparing changes in outcomes from baseline to a fixed time point (e.g. 2, 5 or 10 years) we will use ANOVA combined with post-hoc testing for continuous outcomes. For categorical outcomes we will use standard chi-square analyses. If there is a need for confounder adjustment we will estimate the proper regression models dependent on the level of measurement of the dependent variable. Multilevel models might be used to analyse repeated measures data.

When trying to identify factors that could serve as predictors for outcome we will estimate multivariable regression models. The following factors are a priori considered to be the most relevant: treatment group, age, sex, BMI, smoking, preoperative dural sac cross-sectional area (in mm^2), percentage achieved decompression, preoperative ODI-score and preoperative NRS-score for leg pain and back pain. Bayesian information criterion (BIC) might be used as a statistical tool to select the best performing model.

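### Missing 2-year ODI is governed by two inconsistent rules, carry-forward in the protocol and a 15% imputation trigger in the SAP, and neither is a sound primary rule

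*Combined protocol and SAP*

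**What the plan says.** The primary outcome is change in ODI from baseline to 2 years, and ODI is also collected at 3 and 12 months (SAP, Outcome assessment and Primary outcome). Both documents claim intention to treat.

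- **Protocol, Statistics:** "Dropouts will be registered with the last value before dropout (last value carried forward". No threshold is attached.
- **SAP, Sample size:** "If the number of drop-out or missing data exceeds 15%, imputation will be performed". It gives no method, does not say whether the 15% is counted overall or per arm, names no visit, and is silent on what happens at or below 15%.
- **SAP, Statistical analyses:** continuous outcomes are compared by ANOVA on change at a fixed time point with post-hoc tests. The only repeated-measures provision is permissive: "Multilevel models might be used to analyse repeated measures data".

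The SAP describes itself as a supplement to the protocol (Administrative Information). Its stated reason for revision concerns only the ODI entry threshold. It does not say which document prevails on missing data. The one sensitivity analysis described, in the protocol, deals with crossovers.

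**The concern.** At or below 15% missing, the protocol fills in values and the SAP does not. Above 15%, the SAP imputes by an unnamed method. How missing data on the primary endpoint are handled is therefore not uniquely fixed in advance, and part of the choice depends on the dropout rate once it is known.

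The rules are also weak in themselves. Carry-forward gives anyone lost before 3 months a change of zero, gives later dropouts an early postoperative score, and counts filled values as real 2-year observations. Restricting the ANOVA to patients with a 2-year score discards what is known about the others at 3 and 12 months. The 15% figure is the dropout allowance from the sample size calculation. It says how many completers are needed for power, not that bias below that level is negligible. The trial is open label with non-blinded coordinators, so differential dropout is a realistic risk, although no figure in the documents shows that it is expected.

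**Working it through.** **1. The plan's own figure.** Inputs from SAP Sample size: difference 7, SD 18, alpha 0.02, power 80%, dropout 15%. Sidedness is not stated; two-sided is assumed because it comes close to the stated figure and one-sided does not.

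n = 2 × (2.326 + 0.842)² × 18² / 7² ≈ 133 evaluable per group, and 133 / 0.85 = 156.5, so 157 against the stated 155. From the protocol's own 131 evaluable: 131 / 0.85 = 154.1, rounding up to 155. (One-sided gives 111, or 131 after inflation.) The figure reproduces within 2 patients. Power with 131 completers per group is 79.4%, so planned power already rests on completers. The 15% in the trigger is this same allowance.

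**2. What the trigger lets through.** Counted overall, 0.15 × 465 = 69.75. So 69 missing (69 / 465 = 14.8%) does not trigger imputation and 70 (15.05%) does. Per arm, 0.15 × 155 = 23.25, so 23. An overall count ignores balance: 51, 9 and 9 missing also totals 69, which is 51 / 155 = 33% in one arm and 9 / 155 = 6% in the others. That split is extreme and serves only to show what the rule cannot see.

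**3. Illustrative bias (assumptions, not document figures).** Let m be the missing fraction in an arm and g the amount by which its dropouts do worse than its completers. Complete cases overstate an arm's mean improvement by m × g, so the bias in the contrast of arms A and B is m_B × g_B − m_A × g_A.

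Take 15% versus 5% missing. With 10% in the third arm the overall rate is (15 + 5 + 10) / 3 = 10%, so nothing triggers.

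- Complete cases, g = 5 to 10 in both arms: (0.15 − 0.05) × 5 to 10 = 0.5 to 1.0 point, in favour of the arm with more loss.
- Carry-forward, all losses before 3 months, completers improving by 20 in both arms: (0.15 − 0.05) × 20 = 2.0 points against the arm with more loss, or 2.0 / 7 = 29% of the target difference. All of this is bias if dropouts would have done as well as completers. If they would have done 5 to 10 points worse, the bias is 2.0 − 0.5 = 1.5 down to 2.0 − 1.0 = 1.0.
- On these same data the two analyses differ by 2.0 points whatever the dropouts would have scored.

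Balanced cases: with 15% missing in both arms and equal gaps, complete-case bias is 0; with a gap of 10 in one arm only it is 0.15 × 10 = 1.5. With equal 15% loss and baseline carried forward, bias is 0 when there is no true difference, but a true 7 shrinks to 7 × 0.85 = 5.95.

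**4. A milder scenario.** A simulation assumed mean ODI of 40 at baseline and 20 at 3 and 12 months, SD 18, equal correlation 0.6 between visits, and dropout after 12 months driven by the 12-month score. With no later worsening, carry-forward was biased by about 0.4 to 0.5 points at 10% versus 20% dropout and about 0.9 at 5% versus 25%; with 3 points of worsening by 2 years, by about 0.1 to 0.3. Complete cases were essentially unbiased. That follows from the set-up: with equal correlations, the covariance of the 12-month score with (2-year minus baseline) is 0.6 − 0.6 = 0 in SD² units, so dropout is unrelated to change.

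**5. Precision.** With 15% missing in both arms, 155 × 0.85 = 131.75 observed. Treating 155 as observed with unchanged SD gives an SE ratio of √(131.75 / 155) = 0.922, about 8% below the completers-only SE.

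**The case against.** The best defence is that the SAP is plainly the later text. It cites a 2017 publication, plans 465 patients where the protocol plans 561, and changes the randomisation window and the responder threshold. A reader would probably take its missing-data rule as current too. The carry-forward sentence also follows directly on the crossover sensitivity analysis and could be read as belonging to it, or carry-forward could be the SAP's unnamed method above 15%. These readings narrow the conflict to 15% or less. They do not remove it, because nothing withdraws carry-forward and the SAP's own rule remains incomplete.

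Some stronger inferences are tempting and not supported:

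- *That the SAP prescribes a complete-case analysis.* It never says so. This is a strong inference from the trigger and the fixed-time ANOVA, and the optional multilevel model could use the earlier scores.
- *That neither rule can give a valid intention-to-treat estimate.* Complete cases are unbiased if data are missing completely at random, or if missing fractions and gaps match across arms. Carry-forward is unbiased if ODI is stable after the last visit or the errors cancel.
- *That omitting patients without a 2-year score contradicts the intention-to-treat statement.* The protocol explains that principle by keeping crossovers in their randomised arm, which missing outcomes do not breach.

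It is also fair that every bias figure needs assumed differential or outcome-related dropout, and that the 8% is measured against completers only, whereas a mixed model would legitimately recover some of that precision.

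**Conclusion.** The concern holds in this form: the two documents handle missing 2-year ODI inconsistently, the SAP's rule is incomplete on either side of 15%, and both routes rest on strong unstated assumptions with no missing-data sensitivity analysis behind them. The documentary part needs no assumptions. The numerical part does: biases of roughly 0.5 to 2 points against a 7-point target arise under a 10-percentage-point difference in dropout, the upper end requiring early loss and a 20-point mean improvement. Under balanced missingness and no true difference the bias is near zero. A reader should not conclude that the trial's estimate will be biased, only that the plan neither fixes one method nor guards against bias. Because this concerns the primary endpoint and a better method can use data already scheduled, it should be settled before analysis.

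**What to change.** State expressly that the protocol's carry-forward rule and the SAP's 15% trigger are withdrawn, and give one primary rule that applies at any level of missingness. Either of these would serve:

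- a likelihood-based repeated-measures model for ODI at 3, 12 and 24 months with arm-by-visit terms and baseline ODI, from which the 24-month contrasts are read; or
- multiple imputation using baseline, 3- and 12-month ODI, arm and hospital, followed by the planned comparison.

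The exact covariates are a matter of choice, but they should be fixed in advance. Add one delta-adjusted sensitivity analysis in which imputed scores are made progressively worse, by arm. It should include patients with no follow-up score, whom the repeated-measures model on its own would leave out.

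The cost is a wording change in both documents that alters the primary analysis, plus a little more analysis work. No further visits, data or patients are needed, and the sample size stands.
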